### Data management

Patients’ CRF were sent to the Clinical Research Centre, and data were entered into an Excel spreadsheet. Each record was given a unique identifier consisting of a single digit for the sites and triple digits for the subjects. Data on laboratory findings were obtained from the CPDRL, UiTM in softcopy format and then merged with these records using the unique identifiers. Data cleaning was done to manage outliers, missing values and inconsistencies. The clean dataset labelled as analysis dataset was exported into SPSS and will be made available for reporting the baseline findings. It will be merged with the final visit dataset for definitive analysis.

### Sample size calculation

The sample size calculation was conducted based on the randomised clustered trial design using PASS software (Copyright (c) 2009 by [name], All Rights Reserved).

#### Sample calculation for T2DM patients

A sample size of 626 (313 in each arm) was obtained by sampling 10 clusters (5 intervention vs 5 control) with 63 subjects from each cluster to achieve 91% power to detect 25% difference in the proportion of subjects achieving target HbA1c < 6.5% from baseline and between the intervention and control groups. The test statistic used was the two-sided Z-test (unpooled). The significance level of the test is 0.05. Therefore, after allowing for 25% dropout rate, this study aimed to recruit a total sample of 836 T2DM patients at baseline (i.e. 418 in each arm and 84 from each clinic).

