#### Sample calculation for HPT patients without T2DM

A sample size of 438 (219 in each arm) was obtained by sampling 10 clusters (5 intervention vs 5 control) with 44 subjects from each cluster to achieve 88% power to detect 25% difference in the proportion of subjects achieving target BP < 140/90 mmHg from baseline and between the intervention and control groups. The test statistic used was the two-sided Z-test (unpooled). The significance level of the test is 0.05. Therefore, after allowing for 25% dropout rate, this study aimed to recruit a total sample of 584 HPT patients at baseline (i.e. 292 in each arm and 58 from each clinic).

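### The stated 91% and 88% power omit the limited degrees of freedom from 10 clinics; a test that holds the 5% level on 8 df has about 82% and 78%.

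*Protocol article*

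**What the plan says.** The sample size sections of the protocol article treat the two primary outcomes separately.

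- **T2DM:** "63 subjects from each cluster to achieve 91% power to detect 25% difference in the proportion of subjects" at the HbA1c target. The total is 626, or 313 per arm, from five intervention and five control clinics.
- **HPT without T2DM:** "A sample size of 438 (219 in each arm) was obtained", with "44 subjects from each cluster to achieve 88% power to detect 25% difference in the proportion of subjects" at target.
- **Method, T2DM section (the HPT section uses the same test and level):** "The test statistic used was the two-sided Z-test (unpooled)" and "The significance level of the test is 0.05".
- **HPT recruitment after 25% dropout:** a total of 584, given as "292 in each arm and 58 from each clinic".

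The introduction to these sections says that a cluster-randomised design was used in PASS. Neither an ICC nor a control proportion is given.

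The Statistical analysis section plans a generalised estimating equation (GEE) with an independence working model and Wald chi-square tests. It mentions no small-sample correction. It does say that power will be recalculated for the effect size and the clustering, but it does not mention the small number of clusters.

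**The concern.** In a trial that randomises clinics, the standard error of the treatment effect depends on between-clinic variation. Here that variation is estimated from five clinics per arm, which leaves 10 − 2 = 8 df. The 5% critical value is then 2.306, not 1.96. A power figure based on 1.96 describes a test that does not have a 5% type I error in this design.

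So the stated power and the stated significance level cannot both hold. If the level is enforced, the chance of missing the target effect roughly doubles, from 9% to about 18% for T2DM and from 12% to about 22% for HPT. If the normal reference is kept, the cost is instead an inflated false-positive rate on both primary outcomes.

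**Working it through.** **Inputs from the protocol article.** Two-sided alpha 0.05; unpooled Z-test; 5 clinics per arm; T2DM m = 63 per clinic, n = 313 per arm, power 91%; HPT m = 44, n = 219, power 88%; difference 25%, read as 25 percentage points. ICC and control proportion are not stated.

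**1. Was clustering allowed for?** With n = 313 and n = 219 per arm and no design effect, power for a 25-point difference exceeds 99.9% at every control rate tried (10–40% for T2DM, 50–70% for HPT). A design effect was therefore almost certainly used.

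**2. Can the stated figures be reproduced?** Only with assumed inputs. The formula is

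SE = √{[p0(1 − p0) + p1(1 − p1)] × [1 + (m − 1)ICC] / n}, power = Φ(0.25/SE − 1.96).

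Assume ICC = 0.05. Both 25% vs 50% and 50% vs 75% give p0(1 − p0) + p1(1 − p1) = 0.4375.

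- T2DM: design effect 1 + 62 × 0.05 = 4.10; SE = √(0.4375 × 4.10/313) = 0.0757; 0.25/SE = 3.302; power 91.0%.
- HPT: design effect 1 + 43 × 0.05 = 3.15; SE = √(0.4375 × 3.15/219) = 0.0793; 0.25/SE = 3.152; power 88.3%.

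These match, but other pairs do too. With the article's background control rates (18.1% and 60.1%), the stated powers imply ICCs of 0.057 and 0.065. Over control rates of 10–40% for T2DM the implied ICC runs from 0.046 to 0.075, and over 50–70% for HPT from 0.051 to 0.103.

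**3. Move to 8 df without needing those inputs.** Under the Z-test, the stated power fixes the noncentrality δ = 1.960 + z(power).

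- T2DM: δ = 1.960 + 1.341 = 3.301.
- HPT: δ = 1.960 + 1.175 = 3.135.

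Power of a valid test is P(|T| > 2.306), with T noncentral t on 8 df:

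| Outcome | Stated (Z) | t on 8 df | Range from rounding of the stated power |
|---|---|---|---|
| T2DM | 91% | 82.3% | 81.6–83.0% |
| HPT | 88% | 78.4% | 77.7–79.0% |

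**4. Keep the normal reference instead.** With a variance estimated on 8 df and a cut-off of 1.96, the true two-sided alpha is 2 × P(t8 > 1.96) = 8.6%. Power at the same noncentralities is 89.6% (T2DM) and 86.7% (HPT).

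**5. Simulation check.** Beta-binomial data, 100,000 trials, background control rates and the ICCs they imply (0.057 and 0.065):

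| Test | Power T2DM / HPT | Type I error T2DM / HPT |
|---|---|---|
| Cluster-level t-test, 8 df | 81.5% / 77.8% | 4.8% / 5.1% |
| Uncorrected sandwich-type Wald test | 92.3% / 90.1% | 11.6% / 11.8% |

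**6. HPT count.** 438/0.75 = 584, or 292 per arm; 292/5 = 58.4, printed as 58. Then 58 × 10 = 580 and 580 × 0.75 = 435, against 438 required. For T2DM, 418/5 = 83.6 was rounded up to 84.

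**The case against.** The strongest reply is that the power calculation matches the planned analysis. A GEE Wald chi-square test also uses a normal reference, and step 4 shows that its power stays within about 1.5 points of the stated figures. That stands as far as it goes: if the uncorrected Wald test is used, power is not overstated by some nine points. What is lost is the 5% level, so the risk moves from a missed effect to a false positive. If the full analysis plan contains a small-sample correction that the article does not mention, the level is protected and power falls to the figures in step 3.

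A reader might also infer more than the document supports:

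- **That the calculation ignores the clustering or the 10 clinics.** It does not. Both are in it; only the df adjustment is absent.
- **That the figures are an arithmetic slip.** They are consistent with the method named. The fault lies in the choice of reference distribution.
- **That the planners used an ICC of 0.05.** This is one back-solved possibility. At ICC 0.05 with the background rates of 18.1% and 60.1%, the Z-test would give about 94% and 93%, not the stated figures.
- **That power is far lower still.** An analysis on the five matched pairs (4 df) would give about 70% and 66%, but only if matching removed no between-clinic variance. A larger ICC, or a 12-point effect taken from the cited non-randomised study in private clinics, are separate assumptions that the sample size sections do not make.

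Recruitment and outcome collection were finished at submission, so the sample cannot change. The reported power and the choice of test still can: the article says analysis had only just started.

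**Conclusion.** The point holds. With 5 clinics per arm and a test that keeps the stated two-sided 5% level on 8 df, power is about 82% for T2DM and 78% for HPT, which is 9 to 10 points below the stated values. Alternatively, power stays near the stated level with a true type I error of about 8.6%, or about 12% for an uncorrected sandwich test in simulation.

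The result assumes that the stated powers are correct for the Z-test named, that the difference is absolute, and that the analysis is unpaired. It does not depend on the ICC or control proportion, because the stated power fixes the noncentrality. The loss is moderate: T2DM stays above 80% and HPT falls just below.

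The HPT recruitment figures are inconsistent by 4 patients at baseline and 3 after dropout. The effect on power is negligible.

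**What to change.** - **Power statement.** Keep the sample. Restate power as about 82% (T2DM) and 78% (HPT) for an absolute difference of 25 percentage points, on a t reference with 8 df.
- **Primary test.** In the Statistical analysis section, give the primary comparison a matching small-sample reference or correction: t or F on 8 df for the GEE, or a cluster-level t-test. The restated power is coherent only with this change.
- **Inputs.** Report the ICC and control proportions actually used. The back-solved values above should not be adopted in their place.
- **HPT count.** State 59 per clinic (590 in total), or give the total as 580.

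The cost is a less favourable power statement, a slightly wider confidence interval and one change to the analysis. No extra patients are needed.

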#### Sample calculation for HPT patients without T2DM

A sample size of 438 (219 in each arm) was obtained by sampling 10 clusters (5 intervention vs 5 control) with 44 subjects from each cluster to achieve 88% power to detect 25% difference in the proportion of subjects achieving target BP < 140/90 mmHg from baseline and between the intervention and control groups. The test statistic used was the two-sided Z-test (unpooled). The significance level of the test is 0.05. Therefore, after allowing for 25% dropout rate, this study aimed to recruit a total sample of 584 HPT patients at baseline (i.e. 292 in each arm and 58 from each clinic).

### Statistical analysis

The statistical analysis plan to test the primary hypotheses of the study is described. Continuous variables will be described by summary statistics (means and standard deviations) for normally distributed variables. If the distribution is not normal, median with inter-quartile range will be reported instead. Other descriptive statistics, such as minimum and maximum values will be reported when necessary. Categorical (nominal/ordinal) variables will be described by frequencies with percentages. All outcomes are treated as categorical variables (e.g. proportions of patients achieving targets for HbA1c and BP). To assess the differences in the proportions of patients who are able to reach the treatment goals by their intervention strategy, a generalized estimation equation model that adjusts for clustering effects will be used. The model will be an independent working model. Treatment effects will be obtained using the estimated marginal means and differences will be tested using the Wald chi-square tests. The power of the study will be recalculated based on the effect size and after taking into account the clustering effect of the study design. An intention-to-treat analysis will be conducted, and *P-values* of less than 0.05 will be considered significant. All analyses will be carried out using SPSS (IBM Corp. Released 2011 IBM SPSS Statistics for Windows, Version 20.0. Armonk, NY: IBM Corp.).

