## Methods/Design

This is a pragmatic cluster randomised parallel controlled trial currently being conducted in 10 public primary care clinics in two states in Malaysia—Wilayah Persekutuan Kuala Lumpur (WPKL) and Selangor (SEL). The overall duration of the study is two years, and the duration of intervention is one year. Blinding was not possible due to the nature and complexity of the intervention. The study protocol is registered with clinicaltrial.gov (NCT01545401), and the reporting of this paper has been done in accordance with the CONSORT Statements [36–38].

The cluster randomised trial design was used because of its strengths in evaluating educational and interventional programmes in health care units [38]. The pragmatic study design was chosen to maximise external validity to ensure that the results can be generalised to the public primary care system in Malaysia [39]. The participatory action research (PAR) approach [25, 40] was adopted in the design and implementation of the EMPOWER-PAR intervention to ensure that the primary care providers involved in this study are empowered to choose between actions within their constraints to improve their patients’ health outcomes.

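### With 5 clinics per arm, the planned Wald chi-square tests from an independence GEE do not hold the 5% level: about 12% if matched clinics are uncorrelated, less if they are correlated

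*Protocol article*

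**What the plan says.** The Statistical analysis section presents itself as the analysis plan for the primary hypotheses. It states that "a generalized estimation equation model that adjusts for clustering effects will be used", that "The model will be an independent working model", and that "Treatment effects will be obtained using the estimated marginal means and differences will be tested using the Wald chi-square tests". P-values below 0.05 count as significant. It names no small-sample correction, t or F reference, or clinic-level analysis.

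The number of clusters is fixed elsewhere. The trial is "currently being conducted in 10 public primary care clinics in two states in Malaysia". The T2DM calculation rests on "sampling 10 clusters (5 intervention vs 5 control) with 63 subjects from each cluster" and the HPT calculation on "sampling 10 clusters (5 intervention vs 5 control) with 44 subjects from each cluster". The T2DM sample size section adds that "The significance level of the test is 0.05".

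The Site selection section says that the eligible clinics were matched in pairs on location, staffing and workload, that five pairs were drawn, and that the clinics were then allocated to the arms. Table 1 lists the five pairs. The Statistical analysis section does not mention the pairs.

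**The concern.** Under an independence working model, only the robust (sandwich) variance protects against clustering. That variance is a large-sample quantity in the number of clinics, not patients. With 5 clinics per arm it has two faults. It is biased low, and the chi-square reference treats it as known although it is estimated on only 8 df. Both faults make P-values too small and confidence intervals too narrow.

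This affects the primary test in each of the two patient groups. If the intervention does nothing, the chance of declaring it effective exceeds the stated 0.05 for each hypothesis, unless something else in the design offsets the excess.

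**Working it through.** **Inputs.** From the article: 5 clinics per arm; 63 (T2DM) or 44 (HPT) patients per clinic; two-sided 0.05; independence GEE; Wald chi-square test. Background rates from the Background section, used as null rates in simulation: 18.1% for HbA1c and 60.1% for BP. Assumed, because the article gives no value: ICC, control proportion, variation in clinic size, within-pair correlation. The uncorrected robust variance is also an inference, since the article names no estimator.

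**1. The plan's own power figures.** They cannot be reproduced from stated inputs alone, because neither ICC nor control proportion is given. Assuming 50% vs 75% and ICC 0.05:
- T2DM: design effect 1 + 62 × 0.05 = 4.10; SE = √[(0.25 + 0.1875) × 4.10 / 315] = 0.0755; 0.25/0.0755 = 3.31; power = Φ(3.31 − 1.96) = 91%.
- HPT: design effect 1 + 43 × 0.05 = 3.15; SE = √[0.4375 × 3.15 / 220] = 0.0791; 0.25/0.0791 = 3.16; power = Φ(3.16 − 1.96) = 88%.

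Both match the stated powers.

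**2. Type I error, clinics independent, equal sizes.** With k = 5 clinics per arm, the uncorrected sandwich variance is (k − 1)/k = 0.8 times the unbiased between-clinic variance on 8 df. The Wald z therefore behaves as t₈/√0.8, and

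P(|t₈| > 1.96 × √0.8) = P(|t₈| > 1.753) = **11.8%**.

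This approximation does not involve the ICC, event rate or patients per clinic. The confidence interval has 1.753/2.306 = 0.76 of the width it needs, so it is about 24% too narrow.

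**3. Simulation checks (no effect, nominal 5%).**

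| Setting | Rejection rate |
|---|---|
| T2DM, 18.1%, 63 per clinic, ICC 0 to 0.10, equal sizes | 11.6–12.5% (log-odds scale) |
| HPT, 60.1%, 44 per clinic, ICC 0 to 0.10, equal sizes | 11.2–12.0% (log-odds scale) |
| Either group, assumed CV of clinic size 0.4 | 12.4–14.6% (log-odds scale) |
| Arm-by-time contrast (change from baseline) | 11.6–12.0% |
| Direct GEE fit, T2DM, ICC 0.05 (1,500 trials) | 11.0% (Monte Carlo SE 0.8 points) |

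**4. Which part of the fault matters (equal sizes, independent clinics).**

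| Variance | Normal/chi-square reference | t₈ reference |
|---|---|---|
| Uncorrected (0.8) | 11.8% | 7.3% |
| With factor 10/9 (0.889) | 10.2% | 6.1% |
| Unbiased (1.0) | 8.6% | 5.0% |

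Both the variance and the reference must change to reach 5%.

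**5. Effect of the matching.** The planned test ignores the pairs. A positive correlation ρ between the results of paired clinics shrinks the true variance of the arm difference by (1 − ρ), while the sandwich variance does not shrink. Simulated with normal clinic-level results:

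| Assumed ρ | Planned Wald test | Unpaired t, 8 df | Paired t, 4 df |
|---|---|---|---|
| 0 | 11.7% | 5.0% | 5.0% |
| 0.1 | 10.2% | 4.1% | 5.0% |
| 0.2 | 8.7% | 3.3% | 5.0% |
| 0.3 | 7.2% | 2.6% | 5.0% |
| 0.45 | 5.0% | 1.7% | 5.0% |
| 0.5 | 4.3% | 1.4% | 5.0% |

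**6. Power with a t reference.** Same assumed inputs as step 1, noncentral t on 8 df, critical value 2.306: noncentrality 3.31 gives about 83% (T2DM) and 3.16 gives about 79% (HPT). A paired test on 4 df (critical value 2.776), with no pair correlation, gives about 70% and 66%.

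**The case against.** The strongest counter-argument is the matching. A reader might infer that the test has a true error of 12%, or that false positives are more than twice as frequent as stated, without condition. The article does not support that. The clinics were matched, Table 1 shows close pairs, and ignoring positive pair correlation offsets the inflation, fully so at about 0.45. This stands as a limit on the figure. It does not remove the fault: the article gives no correlation, the matching factors were location, staffing and workload rather than baseline control of HbA1c or BP, and unequal clinic sizes push the error upward. A test that holds its level only at one unstated correlation is not controlled.

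A reader might also infer that the GEE treats the patient rather than the clinic as the cluster. Nothing supports this, since the section says that the model adjusts for clustering.

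Finally, the variance estimator is not named, and a separate analysis plan could add a correction. That is fair, but the article does more than stay silent: it names the chi-square reference and the 0.05 threshold. Even with an unbiased variance, that reference gives 8.6% when pairs are uncorrelated. A model-based variance under independence would ignore the clustering altogether.

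**Conclusion.** The concern holds in conditional form. As written, and with the usual uncorrected robust variance, the primary tests do not deliver the stated 5% level with 5 clinics per arm. The type I error is about 12% with no within-pair correlation, somewhat more with unequal clinic sizes, and about 10%, 9% and 7% at assumed correlations of 0.1, 0.2 and 0.3. Above about 0.45 the test becomes conservative instead.

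The direction of the fault at low to moderate pair correlation is secure and hardly depends on the unstated ICC. The single figure of 12% is not secure, because it rests on uncorrelated pairs. Since the fault affects the primary P-value and interval in both patient groups, it should be corrected before the analysis is run.

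**What to change.** Replace the Wald chi-square reference with one prespecified small-sample method for both primary outcomes, and base the confidence intervals on it:

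- keep the independence GEE, with a bias-corrected sandwich variance (Kauermann-Carroll or Mancl-DeRouen) and a t reference on 8 df; or
- use a t-test on the 10 clinic-level, baseline-adjusted proportions (8 df), which needs no special software.

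State how the pairs are handled. The unpaired t-test stays valid but is conservative if pairs are correlated (size about 4.1% at 0.1 and 2.6% at 0.3). A paired clinic-level t-test on 4 df holds 5% throughout but has less power when pair correlation is low. A permutation test within the 5 pairs is not an option at this level, because its smallest two-sided P is 2/32 = 0.0625.

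The change needs no new data, only analysis wording and a little code. It does cost wider intervals and lower power than stated: about 83% instead of 91% for T2DM and 79% instead of 88% for HPT under the assumed 50% vs 75% and ICC 0.05. The Trial status section reports that outcome data are collected and that cleaning and analysis have just begun, so the change should be dated and documented before between-arm results are seen.

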### Ethical considerations

The Ethics committee of UiTM and the Medical Research Ethics Committee (MREC) of the Ministry of Health (MOH) approved the study protocol. Permission from the Family Health Development Division (FHDD) of the MOH and the respective Health District Offices was also obtained prior to the conduct of the study. The study was conducted in accordance with the Declaration of Helsinki and Good Clinical Practice (GCP) requirements [68]. Patient information sheets were distributed, and informed consent was obtained from all participants prior to their study enrolment. For participants who were unable to read, the content of the consent form was read aloud to them, and a copy of the patient information sheet was given to their next of kin with additional explanation given if needed. Confidentiality of personal information was ensured at all times. Subject enrolment was done by the investigators and not the subjects’ attending doctors to reduce subjects’ perceived coercion to participate in the study. Subjects were informed of any immediate results obtained from the study that might affect their care or health.

## Discussion

The EMPOWER-PAR is the first pragmatic randomised controlled trial of multifaceted chronic disease management strategies conducted in the Malaysian public primary care setting. It is expected to yield important new evidence on the improvements of T2DM and HPT clinical outcomes, the two most prevalent chronic diseases being managed in the public primary care sector. The EMPOWER-PAR hypothesised that patients’ clinical outcomes, namely HbA1c, BP, fasting serum lipid, BMI, WC, medication adherence and their perception and experience of receiving chronic disease care would improve with the EMPOWER-PAR intervention. It also hypothesised that improvements would occur at the primary care provider level in terms of the process of care, prescribing pattern and their perceptions, attitudes and experiences regarding the EMPOWER-PAR intervention. This study will also provide a cost-effectiveness analysis of conducting a multifaceted intervention using readily available resources in a resource-constrained setting.

The EMPOWER-PAR is also unique in the sense that it utilised a pragmatic cluster randomised trial design, which is expected to measure the degree of beneficial effect of the intervention in real life clinical practice. In pragmatic trials, a balance between external validity (generalizability of the results) and internal validity (reliability or accuracy of the results) needs to be achieved [39]. The pragmatic trial seeks to maximize external validity to ensure that the results can be generalised [39]. Therefore, the EMPOWER-PAR intervention ensured that it pragmatically utilised resources that are readily available within the system. These include strengthening the roles of allied health personnel in the CDM team, enhancing their skills to support patients’ self-management and reinforcing the utilisation of CPG to support evidence-based decision making. Although the primary outcomes for EMPOWER-PAR were measured at the patients’ level, its pragmatic design required that the intervention be delivered at the primary care providers’ level. This was done to maximise the sustainability of the intervention even after the trial ends. Some flexibility on the implementation of the intervention programme was also allowed in line with the needs and constraints of the clinics. The PAR approach [25] was therefore adopted in designing and implementing the EMPOWER-PAR intervention, where the CDM team were empowered to choose between actions within their constraints to improve their patients’ health outcomes. This process required the active participation of the CDM team from each clinic to design, propose and implement the intervention program. However, monitoring the intervention and ensuring its implementation may pose a great challenge in a pragmatic trial. Constraints within different clinics, such as high staff turnover, high workload and limited consultation time, may influence the ability of CDM team to implement and sustain the intervention. Therefore, if the EMPOWER-PAR intervention is shown to have a significant beneficial effect, it would prove not only that it can work, but also that it does work and may be sustainable in real life.

Ultimately, the results from this study will provide objective evidence of the effectiveness and cost-effectiveness of a multifaceted intervention based on the CCM in a resource-constrained public primary care setting. If proven effective, the results may be generalisable to other Malaysian public primary clinics that share the same characteristics, and the intervention would probably be inexpensive to replicate. It is hoped that the objective evidence from EMPOWER-PAR will provide a platform to instigate much needed change to the primary health care system in Malaysia.

